## **3.0 Methodology**

### **3.1 Study Type and Design**

This randomised controlled trial (RCT) will be conducted in four primary care clinics in Hulu Langat district which are Klinik Kesihatan Kajang, Klinik Kesihatan Bangi, Klinik Kesihatan Batu 9 and Klinik Kesihatan Balakong. The study duration is 12 months, with recruitment over 6 months. A second follow-up will be conducted one month after providing the InTroDuce-Programme. Two clinics will be randomly assigned to administer the InTroDuce-Programme, while the other two will be provided with standard care, in order to minimise contamination.

(Appendix A: consort diagram)

## CONSORT Flow Diagram

[figure not shown]

## Cluster definition based on urban and suburban classification

Klinik Kesihatan Kajang and Klinik Kesihatan Bangi are classified as urban, while Klinik Kesihatan Batu 9 and Klinik Kesihatan Balakong are classified as suburban. These clinics were selected due to their geographic and demographic similarity, coupled with variability in socioeconomic, educational, cultural, and attitudinal factors. This selection ensures a balanced representation of diverse populations, enhancing the generalizability and applicability of the study findings. The approach is particularly valuable for comprehensively understanding the factors that influence vaccine knowledge and uptake among pregnant mothers.

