## Random Allocation of Clinics

- **Random Assignment:** One clinic from each category (urban and suburban) will be randomly assigned to either the intervention or control group using an online random number generator. This method ensures unbiased allocation and maintains the balance of geographic representation in both groups.
  - **Intervention Clinic:** The clinics will receive the **InTroDuce Programme**, where pregnant women attending the clinic will undergo the educational module on influenza and Tdap vaccination.
  - **Control Clinic:** The clinics will serve as the control group, where pregnant women will receive the standard antenatal care.

**The rationale for Randomization is to minimise contamination.** Randomizing at the clinic level (cluster randomization) rather than at the individual level will help reduce the risk of contamination, where participants in the same clinic may share information or influence each other's behaviour. By assigning entire clinics to either intervention or control, the study ensures that participants within each clinic receive consistent and isolated exposure to the educational materials or standard care.

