### **Questionnaire (Appendix B)**

A validated questionnaire will be used in this study to measure vaccine-related knowledge, attitude and future uptake intention. The questionnaire will be adapted from a study conducted by Hong et al in Singapore (7). There are 6 sections in this questionnaire.

Part A: 3 questions for screening purposes to exclude respondents who did not fulfill the inclusion criteria.

Section 1: 9 items on sociodemographic data and the health status of the respondents.

Section 2: 4 items to assess the knowledge on vaccination in pregnancy.

Section 3: 5 items to assess the knowledge about whooping cough.

Section 4: 4 items to assess the knowledge on Influenza Infection.

Section 5: 2 items to assess attitude towards vaccination in general and in pregnancy.

Section 6: 6 items to assess attitude towards vaccination against influenza and whooping cough during pregnancy.

Content and face validity will be conducted among six experts on the questionnaires.

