### **3.9 Statistical Analysis Plan**

#### **Statistical Methods:**

- a. Primary outcome (knowledge score) will be analyzed using paired t-tests or Mann-Whitney U tests for non-parametric data.
- b. Secondary outcomes (vaccination uptake which is yes or no) will be analyzed using multiple logistic regression to determine the factors associated with no vaccination uptake intention.

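### The primary knowledge analysis names tests that take no covariates, so chance differences in composition between two clinics per arm pass unadjusted into any between-arm comparison and precision is lost

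*Protocol*

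**What the plan says.** **Design.** Section 3.1 of the protocol states: "Two clinics will be randomly assigned to administer the InTroDuce-Programme, while the other two will be provided with standard care". Under Random Allocation of Clinics the draw is made within class: "One clinic from each category (urban and suburban) will be randomly assigned to either the intervention or control group". The unit is the clinic: "Randomizing at the clinic level (cluster randomization) rather than at the individual level".

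**Clinics.** Under the cluster definition in 3.1: "These clinics were selected due to their geographic and demographic similarity, coupled with variability in socioeconomic, educational, cultural, and attitudinal factors". The sentence asserts both similarity (geographic, demographic) and variability (socioeconomic, educational, cultural, attitudinal).

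**Balance claim.** Random Allocation of Clinics says: "This method ensures unbiased allocation and maintains the balance of geographic representation in both groups".

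**Data available.** The questionnaire description in 3.5 lists: "Section 1: 9 items on sociodemographic data and the health status of the respondents". Section 3.6 has the knowledge questionnaire completed before and after the intervention, so a baseline score exists.

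**Analysis.** Section 3.9(a) states: "Primary outcome (knowledge score) will be analyzed using paired t-tests or Mann-Whitney U tests for non-parametric data". The only multivariable model is in 3.9(b). It is for the yes/no secondary outcome, which "will be analyzed using multiple logistic regression to determine the factors associated with no vaccination uptake intention". Its stated purpose is to find associated factors, not to adjust the comparison of arms.

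**The concern.** Stratification balances urban/suburban class and nothing else. Other clinic characteristics fall as the single draw decides, and with two clinics per arm they may fall unevenly. Recruiting more women per clinic does not shrink that imbalance.

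The protocol itself ties such characteristics to the outcomes. Its secondary outcomes include socio-demographic factors that influence outcomes, and specific objective 5 names age, race, income and education in relation to low future uptake. If the intervention clinics happened to serve more educated women, part of a one-month difference in knowledge could reflect that.

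The tests in 3.9(a) cannot respond to this. A Mann-Whitney test of the arms takes no covariate. A paired t-test removes each woman's own baseline level, but it compares before with after inside one group and gives no between-arm estimate. Information that predicts the score, and so would reduce residual variance, is collected and left unused in the primary analysis.

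**Working it through.** **1. The plan's own figure.** Section 3.4: 216 × 1.3 = 280.8, rounded to 281; 281 / (1 − 0.20) = 351.25, giving 351. This reproduces. The evaluable number is 281, about 140 per arm and 281 / 4 = 70.25 per clinic.

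**2. What the allocation can balance.** One clinic per class goes to each arm, so there are 2 × 2 = 4 possible allocations, in two mirror-image pairs. Let dU and dS be the differences in some characteristic within the urban pair and the suburban pair. The absolute arm imbalance is |dU + dS| / 2 or |dU − dS| / 2. Unless both differences are zero, at least one of these is not zero.

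**3. How large an imbalance might be (assumption).** The protocol gives no clinic-level figures. Assume a clinic SD, s, of 10 to 15 percentage points in the share of women with tertiary education.
- Ignoring stratification, the SD of the arm difference is √(s²/2 + s²/2) = s. The chance of a difference of 15 points or more is P(|Z| ≥ 1.5) = 0.134 at s = 10 and P(|Z| ≥ 1.0) = 0.317 at s = 15.
- Only variation within class matters under the stratified draw. If class explained half the clinic variance (assumption), the SD is s/√2. The chances fall to P(|Z| ≥ 2.12) ≈ 0.03 and P(|Z| ≥ 1.41) ≈ 0.16.

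**4. Effect on a post-only comparison.** Assume tertiary-educated women score 0.5 SD higher. An imbalance of 0.15 to 0.20 shifts the arm difference by 0.5 × 0.15 = 0.075 SD to 0.5 × 0.20 = 0.10 SD.

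**5. Scale.** The detectable difference at 80% power and two-sided 5%, with the protocol's design effect, is 2.80 × √(2 × 1.3 / 140) = 0.38 SD. Then 0.075 / 0.38 ≈ 20% and 0.10 / 0.38 ≈ 26%. If clustering is ignored, the detectable difference is 2.80 × √(2 / 140) = 0.335 SD and the shares are 22 to 30%. The first pair is the fairer one, since the protocol itself applies 1.3.

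**6. A second route, through between-clinic variance.** A design effect of 1.3 at 70.25 women per clinic implies an ICC of 0.3 / 69.25 = 0.0043. With two clinics per arm, all clinic differences together move the arm difference by an SD of √ICC (in units of the total SD): 0.07 at 0.0043, and 0.14 at an assumed ICC of 0.02. The standard error that ignores clinic is √(4 / 281) = 0.12 SD. Composition is one component of this variation, so these figures are not additional to those in step 4.

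**7. What adjustment buys.** A simulation with no intervention effect used 70 women per clinic and assumed baseline-to-follow-up correlations of 0.8 (clinic effects) and 0.5 (individual scores). Adding baseline score to an analysis that ignores clinic gave:

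| Assumed ICC | SD of arm difference, unadjusted → adjusted | False-positive rate at nominal 5%, unadjusted → adjusted |
|---|---|---|
| 0.02 | 0.186 → 0.142 | 21.5% → 15.4% |
| 0.05 | 0.245 → 0.175 | 34.8% → 25.5% |

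Adjustment helps but does not restore the nominal error rate, so clinic must also be allowed for. The simulation covers baseline score only. The extra gain from socio-demographic covariates was not quantified.

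**The case against.** **The clinic sentence is ambiguous.** It also asserts demographic similarity, and the text that follows speaks of diverse representation and generalisability. The variability could lie within the sample as a whole rather than between clinics. This stands. A reader might infer that the protocol concedes its arms will be unequal, but the text does not say that.

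**Composition is not a separate bias.** Under random allocation, chance differences in composition are part of between-clinic variance, and a valid clinic-level analysis carries them in its standard error. This stands. A reader might infer a confounding bias over and above clustering, but the design does not support that. What remains is that 3.9(a) neither adjusts for these differences nor allows for clinic.

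**The illustration is generous.** In a before-after change, a stable effect of education on the level of the score cancels, and only differential learning remains. Stratification also lowers the chance of imbalance (step 3). Both stand, so the 0.075 to 0.10 SD applies to a post-only comparison, and its inputs are assumptions.

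**The balance claim is overstated.** A reader might infer this from Random Allocation of Clinics, but that paragraph claims geographic balance only, which the stratified draw delivers.

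**Covariates belong in the SAP, and an unadjusted primary analysis is a legitimate choice.** This fails in part. Choosing covariates is often left to a SAP, but section 3.9 bears that title and names the primary tests. Those tests exclude adjustment, so this is a method fixed badly and not a detail left open.

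**Conclusion.** The point holds as a weakness in the specified primary analysis, worth correcting before results are seen. It rests on three things in the protocol: two clinics per arm stratified only by urban/suburban class, stated variability among the clinics alongside stated similarity, and named tests that take no covariates although baseline score and socio-demographic data are collected. The consequence is that composition differences enter any between-arm comparison of knowledge unadjusted, with loss of precision.

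The size cannot be determined from the document. The 20 to 26% of the detectable difference is an illustration that depends on the assumed education imbalance, the assumed 0.5 SD effect and a post-only comparison. It does not show that the trial's result will be biased by that amount.

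**What to change.** In 3.9(a), replace the named tests with a prespecified between-arm comparison of the one-month knowledge score, adjusted for baseline score and individual-level age, ethnicity, income and education, in an analysis that allows for clinic. One suitable form has two stages: an individual-level regression on these covariates without arm, then a comparison of clinic-level mean residuals between arms. Individual-level covariates then use none of the few between-clinic degrees of freedom. Report the unadjusted result as supportive. Confirm that the four covariates are among the Section 1 items; objective 5 names them, with race for ethnicity.

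State two limits in the text. Adjustment reduces chance imbalance without removing it, and cultural and attitudinal differences are only partly reached by these covariates. At most 4 − 2 = 2 between-clinic degrees of freedom remain, where the two-sided 5% critical t value is 4.30.

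Random Allocation of Clinics needs no change on this point. The cost is protocol wording and a little more analysis, with no new data.

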## Random Allocation of Clinics

- **Random Assignment:** One clinic from each category (urban and suburban) will be randomly assigned to either the intervention or control group using an online random number generator. This method ensures unbiased allocation and maintains the balance of geographic representation in both groups.
  - **Intervention Clinic:** The clinics will receive the **InTroDuce Programme**, where pregnant women attending the clinic will undergo the educational module on influenza and Tdap vaccination.
  - **Control Clinic:** The clinics will serve as the control group, where pregnant women will receive the standard antenatal care.

**The rationale for Randomization is to minimise contamination.** Randomizing at the clinic level (cluster randomization) rather than at the individual level will help reduce the risk of contamination, where participants in the same clinic may share information or influence each other's behaviour. By assigning entire clinics to either intervention or control, the study ensures that participants within each clinic receive consistent and isolated exposure to the educational materials or standard care.

## 3.2 Participants

- **Inclusion Criteria:**
  - Pregnant women aged 18 years and older
  - Before or equal to 32 weeks of gestation as we need to follow-up the patients again at 36 weeks of gestation before delivery occurs.
  - Able to understand and consent to participation in the study.
- **Exclusion Criteria:**
  - Pregnant women with severe anaphylactic or allergic reactions to previous dose of influenza or Tdap vaccination.
  - Non-Malaysian

## Intervention

- **Intervention Group:** Participants will undergo the InTroDuce Programme, which includes an educational module delivered via website. The module will cover:
  - Importance of vaccination for both pregnant women and infant
  - Safety and efficacy of the influenza and Tdap vaccines.
  - Timing of vaccination.
  - Addressing common concerns and misconceptions.
- **Control Group:** Participants in the control group will receive the standard antenatal care

### 3.3 Study Population

All pregnant women attending Klinik Kesihatan Kajang, Klinik Kesihatan Bangi, Klinik Kesihatan Batu 9, and Klinik Kesihatan Balakong during the period of 1st May 2025-30th April 2026.

#### 3.3.1 Inclusion Criteria

1. Pregnant women aged 18 years and older
2. Before or equal to 32 weeks of gestation as we need to follow-up the patients again at 36 weeks of gestation before delivery occurs.
3. Able to understand and consent to participation in the study.

#### 3.3.2 Exclusion Criteria

1. Pregnant women with severe anaphylactic or allergic reactions to previous dose of influenza or Tdap vaccination.
2. Non-Malaysian

#### 3.3.3 Withdrawal Criteria

Subjects can choose to withdraw at any time. Withdrawn subjects will not be replaced.

### 3.4 Sample Size

The sample size was calculated using openEpi software based on earlier study which demonstrated proportion of 55% in intervention group (website with vaccine information) and 36% in control group (usual care) (14) The final sample size is 351 based on the design effect of 1.3, 20% of non-response rate, 95% CI, 80% of power and significant value of 0.05.

| Examples                                 | Sample Size: X-Sectional, Cohort, & Randomized Clinical Trials |        |                |
|------------------------------------------|---------------------------------------------------------------------------|--------|----------------|
| Help                                     |                                                                           |        |                |
| Two-sided significance level(1-alpha):   |                                                                           |        | 95             |
| Power(1-beta, % chance of detecting):    |                                                                           |        | 80             |
| Ratio of sample size, Unexposed/Exposed: |                                                                           |        | 1              |
| Percent of Unexposed with Outcome:       |                                                                           |        | 36             |
| Percent of Exposed with Outcome:         |                                                                           |        | 55             |
| Odds Ratio:                              |                                                                           |        | 2.2            |
| Risk/Prevalence Ratio:                   |                                                                           |        | 1.5            |
| Risk/Prevalence difference:              |                                                                           |        | 19             |
|                                          | Kelsey                                                                    | Fleiss | Fleiss with CC |
| Sample Size - Exposed                    | 109                                                                       | 108    | 118            |
| Sample Size-Nonexposed                   | 109                                                                       | 108    | 118            |
| Total sample size:                       | 218                                                                       | 216    | 236            |

Design effect= 1.3

216x 1.3=281

Taking into consideration non-respondent rate of 20%, final sample size is 351.

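### Section 3.4 claims 80% power with no allowance for two clinics per arm; a clinic-level analysis on 2 degrees of freedom has about 36%, even at the plan's own design effect of 1.3

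*Protocol*

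**What the plan says.** Section 3.4 takes 55% in the intervention group and 36% in the control group from an earlier study. The sample size output is two-sided at 95% confidence with a 1:1 ratio and shows 108 per group (216 in total) by the Fleiss method without continuity correction. The clustering step is one line, "Design effect= 1.3", which turns 216 into 281. Allowing for 20% non-response then gives 351. The claim attached to that number is "The final sample size is 351 based on the design effect of 1.3, 20% of non-response rate, 95% CI, 80% of power", and the same sentence sets the significance level at 0.05.

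The design is set out in section 3.1: "Two clinics will be randomly assigned to administer the InTroDuce-Programme, while the other two will be provided with standard care". Under the heading on random allocation of clinics, each arm gets one urban and one suburban clinic, and the protocol calls this cluster randomisation. Section 3.9 names paired t-tests or Mann-Whitney tests for the knowledge score, which it calls primary, and multiple logistic regression for yes/no uptake, which it calls secondary. None of these is described as a clinic-level or cluster-adjusted analysis.

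**The concern.** A design effect inflates the variance of the treatment difference. It does not account for how poorly the between-clinic variance is estimated when there are only two clinics per arm. With many clusters that omission is harmless, because the critical value stays near 1.96. With four clusters the critical value is 4.30, and power falls sharply at any ICC.

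The 1.3 also cannot be judged as it stands, because a design effect has no meaning without the ICC and cluster size behind it.

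At stake is how the result will be read. A reader who believes the 80% will take a non-significant result as fair evidence that the programme does not produce a 19-point gain. On four clinics it would not be.

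**Working it through.** **Inputs from the protocol.** Proportions 0.36 and 0.55 (difference 0.19); two-sided alpha 0.05; design effect (DE) 1.3; 281 analysed and 351 enrolled; four clinics, two per arm. **Assumption:** equal clinic sizes.

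**1. The plan's own figure.** The Fleiss formula without continuity correction gives 107 per arm, against 108 in the protocol. With 108 per arm, individually randomised power is 80.5%. Then 216 × 1.3 = 280.8 (281), and 280.8 / 0.80 = 351. The figure reproduces.

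**2. ICC implied by 1.3.** From DE = 1 + (m − 1) × ICC:
- 281 / 4 = 70.25 per clinic: ICC = 0.3 / 69.25 = 0.0043
- 351 / 4 = 87.75 per clinic: ICC = 0.3 / 86.75 = 0.0035

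**3. Standard error at DE 1.3, 281 analysed.** The variance sum is 0.36 × 0.64 + 0.55 × 0.45 = 0.4779, with 140.5 women per arm. SE = √(0.4779 × 1.3 / 140.5) = 0.0665, so 0.19 / 0.0665 = 2.857.

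**4. Power with the between-clinic variance treated as known.** Φ(2.857 − 1.96) = 0.815. This is where the 80% comes from.

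**5. Power when that variance is estimated from four clinics.** df = 4 − 2 = 2, critical value 4.303, noncentral t with noncentrality 2.857: power 0.362. A simulation with beta-binomial clinic outcomes, 70 women per clinic, a t-test on the four clinic proportions and 400,000 replicates gave 0.363, with type I error of 0.049. If the urban/suburban stratum is also fitted, 1 df remains (critical value 12.71) and power is 0.177.

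**6. Precision.** The 95% half-width on 2 df is 4.303 × 0.0665 = 0.286, about 29 points. Using 1.96 it would be 0.130, or 13 points.

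**7. All 351 analysed, 2 df.** Power is 0.406 at ICC 0.0043 (DE 1.376), or 0.422 if DE stays at 1.3.

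**8. Individual-level test ignoring clustering.** At DE 1.3 the two-sided type I error is 2 × [1 − Φ(1.96 / √1.3)] = 0.086.

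**9. Larger ICCs (assumed; the protocol gives none), 281 analysed.**

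| ICC | DE | Power, variance known | Power, 2 df |
|---|---|---|---|
| 0.0043 (implied) | 1.3 | 82% | 36% |
| 0.01 | 1.7 | 71% | 30% |
| 0.02 | 2.4 | 56% | 24% |
| 0.05 | 4.5 | 34% | 15% |

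**10. More women in the same four clinics, 2 df.** At the implied ICC, 1,000 per clinic gives 76%, 80% is crossed between 2,000 and 3,000 per clinic, and the limit is about 83%. At an assumed ICC of 0.02 the limit is 34%.

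**The case against.** The best defence is that 36% belongs to a test the protocol does not name. Section 3.9 lists individual-level methods, and a large-sample calculation at a design effect of 1.3 does give about 82%. It is true that 36% is conditional on a clinic-level analysis with 2 df. But the alternative does not rescue the claim. An unadjusted individual-level test at DE 1.3 would reject about 87% of the time (threshold 1.96 × 0.0583 = 0.114; Φ[(0.19 − 0.114) / 0.0665] = 0.87). It would do so at a type I error near 8.6%, so it does not meet the stated 0.05. A statistical analysis plan may exist and name a clustered analysis. That would not alter the power figure printed in section 3.4.

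Some stronger readings are tempting but not supported:
- A reader might infer that the sample size arithmetic is wrong. It is not; the fault lies in the missing allowance for few clusters and the unexplained 1.3.
- A reader might hold that the protocol contradicts a small ICC because it describes the clinics as "coupled with variability in socioeconomic, educational, cultural, and attitudinal factors". The same sentence says the clinics were selected for geographic and demographic similarity. It does not say that the variability lies between clinics within a stratum, and urban/suburban differences are balanced by the allocation. Nor is an ICC of 0.0043 zero: at these proportions it is a between-clinic standard deviation of about 3.2 points (√(0.0043 × 0.36 × 0.64) ≈ 0.032).
- A reader might infer that 1.3 has been shown to be too small. It has not. The documents give no ICC, and 0.01 to 0.05 are assumptions.
- A reader might say that no enrolment in four clinics could reach 80%. At the implied ICC that is false in principle, though the numbers needed are impractical.

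**Conclusion.** The 80% power in section 3.4 is not delivered by the design in section 3.1. On the protocol's own inputs, with equal clinic sizes and a valid clinic-level comparison on 2 df, power for 55% versus 36% is about 36% with 281 analysed and 41 to 42% with all 351. It is about 18% if the stratum takes another degree of freedom. The expected 95% half-width of about 29 points is wider than the 19-point difference the trial is sized for.

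This conclusion takes the design effect of 1.3 as given, so it does not depend on any ICC from outside the documents; larger ICCs would only lower the power. It does depend on the analysis respecting the unit of randomisation, which the stated alpha of 0.05 requires.

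The calculation also rests on a proportion. In section 3.9 the only yes/no outcome is uptake intention, listed there as secondary, so section 3.4 gives no power for the knowledge score.

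**What to change.** In section 3.4:
- State the ICC, its source and the women per clinic behind 1.3 (about 70 evaluable), and show a range of ICCs.
- Replace the 80% with the power and expected confidence interval half-width for four clinics under a clinic-level analysis on 2 df: about 36% and 29 points at DE 1.3 with 281 analysed.
- Say that the calculation is for the yes/no uptake-intention outcome and not for the knowledge score.
- Say that a non-significant result will not be read as evidence of no effect.
- If enrolment is discussed, say that no practical number of women in the same four clinics restores 80%, with the figures for 1,000 per clinic and for an assumed ICC of 0.02.

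In section 3.9, name the clinic-level analysis on which the restated power rests, so that the two sections agree.

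The cost is protocol wording and a less favourable power statement. No extra participants or clinics are needed for this correction.
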